## Abstract

**Introduction:**

Hospital admissions are shorter than they were 10 years ago. Notwithstanding the benefits of this, patients often leave hospital requiring ongoing care. The transition period can therefore be risky, particularly for older people with complex health and social care needs. Previous research has predominantly focused on the errors and harms that occur during transitions of care. In contrast, this study adopts an asset-based approach to learn from factors that facilitate safe outcomes. It seeks to explore how staff within high-performing (‘positively deviant’) teams successfully support transitions from hospital to home for older people.

**Methods and analysis:**

Six high-performing general practices and six hospital specialties that demonstrate exceptionally low or reducing 30-day emergency hospital readmission rates will be invited to participate in the study. Healthcare staff from these clinical teams will be recruited to take part in focus groups, individual interviews and/or observations of staff meetings. Data collection will explore the ways in which teams successfully deliver exceptionally safe transitional care and how they overcome the challenges faced in their everyday clinical work. Data will be thematically analysed using a pen portrait approach to identify the manifest (explicit) and latent (abstract) factors that facilitate success.

**Ethics and dissemination:**

Ethical approval was obtained from the University of Leeds. The study will help develop our understanding of how multidisciplinary staff within different healthcare settings successfully support care transitions for older people. Findings will be disseminated to academic and clinical audiences through peer-reviewed articles, conferences and workshops. Findings will also inform the development of an intervention to improve the safety and experience of older people during transitions from hospital to home.

Strengths and limitations of this studyInstead of focusing on error and harm, this study adopts a ‘Safety-II’ perspective and applies the positive deviance approach to explore how healthcare professionals support *successful* transitions of care for older patients.Perspectives about how safe transitional care is delivered will be gathered from a wide range of multidisciplinary clinical staff working in a variety of different healthcare settings.This will allow an exploration of both the commonalities and differences that exist across and between different contexts.Problems commonly associated with routinely collected data may limit the extent to which healthcare teams can truly be considered high performers.Focus group and interview methods may not uncover the underlying, latent factors that contribute to successful transitions of care as they rely on the ability of staff to identify and verbalise the ways in which they succeed.

## Background

Healthcare services in the UK are increasingly being delivered within community settings and the average length of a hospital stay is now 2 days shorter than it was 10 years ago.^1^ This aligns with patient preferences to be at home and benefits hospitals by improving flow and enabling them to treat more people. However, shorter lengths of stay mean patients often leave hospital with ongoing care needs that are directly related to their recent hospitalisation, such as wound care treatment, changes to, or monitoring of, new medications and limited mobility associated with deconditioning and inactivity. The risk of complications and the discontinuity of care that occurs between primary and secondary healthcare services increase a patient’s vulnerability to things going wrong.^2^ As many as one in five patients experience an adverse event during the transition from hospital to home, 62% of which could be prevented or minimised.^3^ Emergency hospital readmission rates are the only routinely collected measure of quality at transitions within the English National Health Service (NHS). Since 2012/2013 emergency readmission rates have increased by 22.8% from 372 805 to 457 880^4^ and, although national statistics do not assess preventability, research studies estimate that around 30% of all readmissions are potentially avoidable.^5–7^

Transitions of care are particularly risky for older people with more complex health and social care needs (eg, comorbidities, frailty and cognitive impairments). Given that older people are more likely to be readmitted to hospital^8–10^ and that this population accounts for the majority of NHS patients,^1^ improving the quality and safety of care for older people during transitions is a priority for the UK’s Department of Health. Furthermore, the financial penalties incurred by NHS trusts (secondary care providers) exert economic pressure to reduce emergency hospital readmissions.^11^

The traditional approach to safety management within healthcare, known as Safety-I, has been to focus on past errors and harm.^12^ Most previous research exploring healthcare professionals’ perceptions about the quality and safety of care transitions has adopted this Safety-I approach by highlighting the fundamental and universal system flaws. These include communication breakdowns across professional groups and care settings (exacerbated by poor understanding of mutual roles in the transition), a lack of accountability and poor communication with the patient.^13–17^ Research has sought to understand what goes wrong at transitions of care in order to provide top down guidance on potential solutions. Although useful, this deficit-based approach only tells us about the *absence* of safety. It says nothing about how safe care is delivered successfully, what the solutions to problems may be or whether a chosen solution is likely to be effective.

### Adopting an asset-based approach to safety management

Over the past 5 years, a more positive approach to safety management, commonly known as Safety-II, has been proposed.^12 18^ This approach recognises that healthcare ‘goes right’ far more often than it ‘goes wrong’ and that exploring and maximising how *safe* (rather than unsafe) care is delivered may help to reduce errors and improve safety.

Furthermore, healthcare organisations are considered to be complex adaptive systems.^19^ Autonomous healthcare professionals interact across multiple networks within dynamic, non-linear and self-organising systems that change over time.^20^ Given this complexity, the top down, linear solutions of Safety-I may be less effective. Healthcare professionals interpret and tailor guidelines and procedures—their actions are influenced by networks, unpredictable working environments and the competing bottom up, informal rules to which they work.^21^ As a result, healthcare teams and organisations demonstrate resilience—they respond, monitor, learn and anticipate. It is this intrinsic ability to adjust to changes and disturbances that enables them to successfully deliver patient care under expected and unexpected conditions.^22^

In line with the Safety-II perspective, ‘positive deviance’ provides an asset-based approach to improvement.^23 24^ This approach seeks to identify and learn from individuals, teams or organisations who demonstrate exceptional performance despite facing similar constraints as others. It is increasingly being used within healthcare organisations to improve the quality and safety of patient care,^25 26^ for example, in improving hand hygiene behaviours and reducing healthcare-associated infections.^27 28^

Bradley *et al*^24^ have proposed a four-stage framework to apply the positive deviance approach within healthcare organisations. Routinely collected data are analysed to identify positive deviants who demonstrate exceptional performance on an outcome of interest (stage 1). Qualitative methods are used to generate hypotheses about how positive deviants succeed (stage 2). These ‘positively deviant strategies’ are then tested within larger and more representative samples (stage 3) and then disseminated to others with the help of key stakeholders (stage 4).

### Study aim and research questions

This study applies stage 2 of the positive deviance framework.^24^ It seeks to explore how high-performing teams (general practices and hospital specialties that demonstrate low or reducing readmission rates over time) successfully deliver safe care to older people and demonstrate resilience during transitions from hospital to home. The following research questions will be addressed:What strategies do high-performing teams use to deliver safe transitions of care to older people?What contextual factors are important in facilitating safe transitional care for older people?What challenges are faced when delivering safe transitional care for older people and how do high-performing teams demonstrate resilience to overcome them?

### Preparatory work to identify high-performing teams

In preparation for this study, stage 1 of the positive deviance framework^24^ was conducted to identify high-performing general practices and hospital specialties that demonstrate the lowest or reducing emergency readmission rates over a specified period of time.

The initial study population comprised 151 general practices clustered within five West Yorkshire clinical commissioning groups (CCGs) and 85 hospital specialities clustered within 22 acute NHS Trusts in the North of England. Cardiology, respiratory and medicine for older people specialties were selected as their patient populations are typically older than those of others specialties (eg, general surgery). They were selected following a review of publicly available Hospital Episode Statistics (HES)^29^ and a consensus approach with clinical advisors (a geriatrician, a clinical epidemiologist and two general practitioners (GPs)).

For each general practice and hospital specialty, total numbers of hospital discharges and 30-day emergency readmissions for patients aged 75 years and over were extracted from the NHS Secondary Use Services data repository for primary care^30^ and HES for secondary care.^29^ In primary care, data were extracted over two time frames: April 2015 to March 2016 (for all five CCGs); and April 2016 to January 2017 (for two CCGs) or to February 2017 (for three CCGs). In secondary care, data were extracted over three time frames: 2013/2014, 2014/2015 and 2015/2016 (November to October for all years). These time frames represent the most recent data that were available in each setting.

The 30-day emergency readmission rates for patients aged 75 years and over were calculated for each general practice and hospital specialty. Statistical Process Control methods were then used to analyse the data in both settings.^31 32^ Binomial funnel plots with limits calculated using the Wilson Score method^33^ were created at each time point for the five CCGs and three types of hospital specialty. In both settings, control limits were set at 2 and 3 sigma (σ) and high performers were classed as those teams (general practices or hospital specialties) that exceeded these limits. In addition to learning from those who performed the best in the region, bar charts were also plotted using the secondary care data to identify hospital specialties with reducing readmission rates, that is, those with improved performance over time. It was difficult to apply definitive rules to this as data varied markedly between hospital sites and specialties. As such, the researchers discussed the data as a group and selected the high-performing hospital specialties that demonstrated the greatest reduction in readmission rates over the 3-year period. Findings from this preparatory work were used to select a sample of high-performing general practices and hospital specialties for this study.

## Method

### Sampling the high-performing teams

A diverse group of high-performing general practices and hospital specialties will be purposively sampled during this study to explore how success is achieved across a range of different healthcare contexts. High-performing general practices that exceed the funnel plot control limits will be purposively sampled using publicly available data for four variables: the practices’ total list size (number of patients); a practice level measure of deprivation; the proportion of patients aged 75 years and over and the proportion of patients in a nursing home.^34^ General practices will be dichotomised for each variable (above and below average).

In secondary care, the clinical leads from high-performing specialties that either consistently exceeded the funnel plot control limits (over 2 or 3 years), or showed a reduction in readmission rates over time will be approached for a brief telephone conversation (~15 min). The aim of these will be to better understand whether there are any likely explanations, other than their teams performing well, which might explain their high performance (eg, data coding anomalies—see online supplementary file 1 for a topic guide). Specialties will then be purposively sampled using the following criteria:To equally represent all three specialties (cardiology, respiratory medicine and geriatric medicine) and the two manifestations of ‘high performance’ (exceed funnel plot control limits vs improvement over time).To represent specialties that care for patients from a range of different socioeconomic backgrounds—as measured by Index of Multiple Deprivation data at NHS Trust level.^35^
Where relevant, to represent specialties from secondary and tertiary services (eg, cardiology).

10.1136/bmjopen-2018-022468.supp1Supplementary file 1

High-performing specialties may perform exceptionally well simply because their patients are kept in hospital for longer periods of time and thus have fewer needs on discharge. Length of stay (LoS) data are not publicly available at individual hospital specialty level, therefore, it was not possible to control for this in the preparatory work. To exclude the possibility that high-performing specialties have low readmission rates simply because their patients have exceptionally long hospital stays, LoS data for each participating specialty will be descriptively compared with the publicly available national LoS average for each specialty during the period of 2015/2016.^1^

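### A length-of-stay comparison for 2015/2016 alone cannot exclude longer stays as the reason for low or falling readmissions judged over three years

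*Protocol article*

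**What the plan says.** Under Method, Sampling the high-performing teams, the protocol article recognises that a specialty may have few readmissions because it keeps patients in longer. It explains that specialty-level LoS is not public, so that "it was not possible to control for this in the preparatory work". It then sets out a later check whose purpose is given as "To exclude the possibility that high-performing specialties have low readmission rates simply because their patients have exceptionally long hospital stays". The check itself is: "LoS data for each participating specialty will be descriptively compared with the publicly available national LoS average for each specialty", "during the period of 2015/2016".

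The selection that this check is meant to support covers a longer period. Under Background, Preparatory work to identify high-performing teams: "In secondary care, data were extracted over three time frames: 2013/2014, 2014/2015 and 2015/2016 (November to October for all years". There are two routes to being called high-performing in secondary care. A specialty either "consistently exceeded the funnel plot control limits (over 2 or 3 years", or was picked for improvement, where the researchers "selected the high-performing hospital specialties that demonstrated the greatest reduction in readmission rates over the 3-year period". The sampling criteria ask for the two routes to be equally represented.

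Before sampling, clinical leads are telephoned to learn "whether there are any likely explanations, other than their teams performing well, which might explain their high performance". Coding anomalies are the example given.

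**The concern.** The plan identifies a specific confounder, says it could not be handled when the high performers were identified, and relies on one named comparison to rule it out. That comparison uses a different time window from the selection. For half of the intended hospital sample it also measures a level where the rival explanation is about a change.

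The study's premise is that these teams are positive deviants. Their practices become themes, and the themes help to shape an intervention that later goes into a randomised trial (Discussion). If a specialty's readmissions were low or fell because stays were longer, its reported strategies could be credited with a result that came from elsewhere. A reader told that long stays had been excluded would have no reason to look for this.

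**Working it through.** No figure in the document can be reproduced here: it gives no LoS, no readmission rate by specialty and no discharge volume. The check is to set selection and LoS comparison side by side.

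| | Selection as high-performing | LoS comparison |
|---|---|---|
| Period | 2013/2014, 2014/2015, 2015/2016 | 2015/2016 |
| Quantity | Low rate in 2 or 3 years, or fall over 3 years | Level in one year |
| Age group | 75 and over | No age limit stated |
| Units | 85 specialties screened | Participating specialties, at most 6 |
| Reference | Funnel limits, or the specialty's own earlier rates | National average for the specialty |

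**Improving specialties.** The rival explanation is that LoS rose while readmissions fell. Testing it needs at least two time points, LoS at the start and at the end of 2013/2014 to 2015/2016. The plan has one. Take a specialty whose stays moved from short to average over the three years. In 2015/2016 it sits at the national average and passes the comparison, yet the lengthening of stays could account for its fall in readmissions. Conversely, a specialty with long but unchanged stays would look suspect, although unchanged LoS cannot explain a fall. For this route the single-year level can mislead in both directions.

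Number affected: the maximum is 6 hospital specialties, and equal representation of two routes gives 6 / 2 = 3 improving sites. This is the planned split; the realised one is not reported.

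**Consistently low specialties.** Here the level of LoS is the right quantity, but it is seen for one year. If a specialty qualified on three years, 1 of 3 is checked. If it qualified on two, 1 of 2 is checked, or none should those two years be 2013/2014 and 2014/2015. The article does not say which two years count. A 2015/2016 value at or below the national average is genuine evidence against long stays in that year and says nothing direct about the others.

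**Age.** Readmissions are counted in patients aged 75 and over. The article states no age limit for either side of the LoS comparison. This is silence, not a stated mismatch, but it needs settling when the data are requested.

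**Limitations section.** Discussion, Strengths and limitations, lists coding, commissioning and the validity of readmissions as an outcome, and does not name LoS. It offers the inclusion of improving specialties as a response to such limitations. Comparing a site with its own past does remove stable differences between sites. It does not remove a change in LoS, and this is the group in which the planned check cannot detect one.

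**The case against.** The best defence is that the check is modest by design. It looks for exceptionally long stays, not for LoS-adjusted performance. It covers the right units, since only participating teams supply themes. Specialty-level LoS was not public, so nothing could be done at identification. The study is qualitative and hypothesis-generating, its findings are combined with other work packages and the literature, and the article already warns that routine data may limit how far teams are truly high performers. All of this stands. It lowers the severity and shows that the check has some value. It does not answer the time-window problem, which rests on what the article states and not on what it leaves out.

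Several stronger readings are tempting, and the documents do not support them:

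- *A long-stay site would simply be kept.* The article gives no threshold or consequence, but it condenses a fuller protocol that is not shown and may contain one.
- *LoS was ignored before sampling.* The telephone call asks openly about other explanations, coding is only an example, and the topic guide is in a supplement not shown. LoS may have been raised.
- *LoS alone could supply a large share of the funnel-plot signal.* Any such figure needs a baseline rate, a volume, an excess stay and an effect per day. None is in the documents, and the answer moves widely with the values chosen.
- *The check should be moved ahead of sampling and long-stay sites replaced.* Study design and status says site recruitment was complete by the end of May 2018, so this would mean reopening recruitment.

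**Conclusion.** The point holds at moderate severity. A descriptive comparison of participating specialties in 2015/2016 gives weak evidence against grossly long stays in that year. It does not exclude LoS as an explanation for performance judged over 2013/2014 to 2015/2016. For improving specialties, about three of at most six hospital sites under equal representation, it cannot address the rival explanation, because one year shows no change. For consistently low specialties it covers at most one of the two or three selection years.

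The conclusion assumes that 2015/2016 is the only LoS period used, as the article states. It does not depend on any assumed size of the LoS effect, which cannot be quantified from the documents. A reader might infer that the high-performer labels are invalid. The documents do not show that any site had long or lengthening stays, only that the planned check could miss it.

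**What to change.** 1. Request LoS from each participating hospital specialty for all three November-to-October years used in selection, for patients aged 75 and over where the specialty can supply it.
2. Compare with the best-matched national reference available, and state the age group and year boundaries of both sides.
3. For improving specialties, show the change in LoS next to the change in readmissions over the same years.
4. Flag any site whose LoS was clearly long, or rose as readmissions fell, and re-examine the themes without it. Write down what counts as clearly long before the data are seen.
5. In Sampling the high-performing teams, change the purpose from *to exclude* to *to assess*. In Strengths and limitations, name residual LoS confounding.

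The cost is one further data request to at most six specialties, a paragraph of wording, and possibly one or two flagged sites. Recruitment need not be reopened. If some specialties cannot supply the earlier years, item 5 still applies, and the report should say which sites were assessed on one year only.

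### The length-of-stay check covers the level in 2015/2016 only, so for hospital specialties sampled on a falling readmission rate it cannot show whether stays lengthened as readmissions fell

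*Protocol article*

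**What the plan says.** Under Preparatory work to identify high-performing teams, hospital readmission data cover three years, 2013/2014 to 2015/2016, each running November to October. One group of specialties was chosen by group discussion as those with "the greatest reduction in readmission rates over the 3-year period".

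Under Sampling the high-performing teams, the clinical leads to be telephoned are those of specialties that either "consistently exceeded the funnel plot control limits (over 2 or 3 years), or showed a reduction in readmission rates over time". The call lasts about 15 minutes and asks about explanations other than good performance. Sampling then aims to represent both kinds of high performance equally. Study design and status sets a maximum of six hospital specialties.

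On length of stay, the protocol says that "it was not possible to control for this in the preparatory work". The remedy is a descriptive comparison of each participating specialty's LoS with the public "national LoS average for each specialty during the period of 2015/2016". Its purpose is given as: "To exclude the possibility that high-performing specialties have low readmission rates simply because their patients have exceptionally long hospital stays". The text shown plans no LoS figure for an earlier year and no within-specialty change in LoS.

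**The concern.** The check and one of the two selection routes measure different things. A specialty on the improvement route is in the sample because its rate changed over three years. The matching rival explanation is that its LoS changed over the same years. The check looks at where LoS stood in the last year.

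The label of high performer is the premise for interviewing these teams. If a fall in readmissions came with longer stays, what staff describe could be credited to transitional care when part of the fall reflects later discharge. The protocol's Strengths and limitations section also presents the improvement route as a response to the difficulty of comparing sites like for like. A comparison of a site's level with a national level brings that difficulty back for the very group meant to ease it.

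**Working it through.** The plan gives no figure to reproduce. The check is a count and a comparison of two quantities.

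**Sites affected.** Two kinds of high performance, equally represented among at most six specialties: 6 / 2 = 3. This is a sampling target, not a reported result.

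**What is seen and what is needed.** Let S be the specialty's LoS and N the national average.

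- Seen by the check: gap = S(2015/16) − N(2015/16).
- Needed for a lengthening explanation: change = S(2015/16) − S(2013/14).

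S(2013/14) is not in the first expression, so the gap does not determine the change. The following figures are assumed, in days relative to the 2015/16 national average:

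| LoS 2013/14 | LoS 2015/16 | Change | Gap seen |
|---|---|---|---|
| −3 | 0 | +3 | 0 |
| −2 | 0 | +2 | 0 |
| −1 | 0 | +1 | 0 |
| 0 | 0 | 0 | 0 |
| +2 | +2 | 0 | +2 |
| −1 | +2 | +3 | +2 |

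The first four rows look identical to the check, although the change runs from 0 to 3 days. The last two also look identical: in one, stays never lengthened and so cannot account for a fall; in the other they rose by 3 days. As a proportion, an assumed rise from 6 to 8 days against a national 8 is 8/6 − 1 = 33%, while the ratio seen is 8/8 = 1.00.

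**National drift.** The Background says average stay is 2 days shorter than 10 years ago. If that decline were linear and applied to these specialties (both assumptions), it is −2/10 = −0.2 day per year, or 2 × −0.2 = −0.4 day from 2013/14 to 2015/16. A specialty with constant LoS would then show a relative rise of 0.4 day with an absolute change of 0. Absolute and relative change must therefore be kept apart.

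**Funnel-plot route.** This group was chosen on a low level, so a level check suits it. Of the three possible pairs of years, one (2013/14 with 2014/15) leaves out 2015/16. A specialty could thus qualify on years that the check does not cover, but nothing shows that any did.

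**The case against.** The stated aim is narrow: to rule out unusually long stays as the reason for low rates. A level comparison answers that, and a specialty that reaches the national average is correctly passed. This stands as a description of the check. However, the aim is worded for low rates, while the check is applied to every participating specialty, including those sampled because the rate fell.

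A reader might infer that improvement-route specialties go wholly unexamined. The documents do not support that. They receive the 2015/2016 comparison, which would flag stays that had become very long by the final year. Their clinical leads are also asked about other explanations. Coding anomalies are only the example given, and the topic guide is in a supplement not shown, so LoS may come up. It remains a short conversation, with no LoS data mentioned.

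The year could be read as attached to the national figure alone, and the full protocol may specify more. The article names no other year for the specialty data, and a comparison with a 2015/2016 average implies the same period.

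The consequence is also bounded. The study generates hypotheses, admits limits in routine data, analyses themes across teams, and combines its findings with other work packages and the literature before an intervention is built. This lowers the stakes but does not make the check able to see a change.

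**Conclusion.** The point holds for the improvement route, about three of six hospital specialties by design. For them, no planned data test whether stays lengthened as readmissions fell; the only other screen is informal. The size of any effect is unknown. The day figures above are illustrations, and the one LoS trend in the protocol is downward. Nothing shows that any sampled specialty did lengthen its stays.

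Two stronger readings should be avoided. For the funnel-plot route, a check falling in a year when the specialty was not low is a possibility, not a demonstrated fault. And a rise in LoS that coincides with a fall in readmissions would not show that LoS caused the fall. Labelling every relative rise that way could also catch a specialty whose stays never changed.

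This is a modest weakness in testing a rival explanation that the protocol itself raises, and a cheap one to repair.

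**What to change.** When specialty LoS is obtained, ask for 2013/14, 2014/15 and 2015/16, or the nearest periods available, since November to October figures may not exist nationally.

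- Improvement route: tabulate the absolute change in LoS, and the change relative to the national average, beside the change in readmission rate.
- Funnel-plot route: show LoS for each year in which the specialty crossed the limit.
- Where a fall in readmissions coincides with an absolute rise in LoS, report longer stays as a possible explanation, and do not rest any facilitating factor on that site alone.

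The cost is two more years of data from at most six specialties and one extra table. The protocol does not say how specialty LoS will be obtained, so the effort for each site is not known. Site recruitment ended in May 2018, so the change bears on interpretation and not on selection. The downside is that a site's high-performer label may need a caveat.
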